#### Statistical analysis

There are 4 measurement times, of which 3 are post-intervention. Linear mixed models will be used to account for the hierarchical, non-independent nature of the data: repeated measures on patients nested within clusters (primary care services). Baseline outcome measures (e.g., HAM-D and GDS-SF) will be used as a covariate, which improves efficiency [52]. These models will allow for 1) comparing patterns of change over time by testing the intervention group by time interaction and 2) estimating and testing differences in outcome measures between groups at time points of interest via linear contrasts. Reporting will follow the CONSORT statement [41].

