**Methods/design:**

The PROMISE-D study is a randomised controlled trial of two evidence-based treatments for late-life major or minor depression for patients who also have at least one co-morbid chronic health problem. Participants will be randomised to two active interventions (PST or CBT) or enhanced treatment-as-usual (E-TAU). Primary outcomes will be depression diagnostic status and severity of depression (according to the Hamilton Depression Rating Scale and the Geriatric Depression Scale). Secondary outcomes will be anxiety severity, quality of life and health care utilisation. Assessments will be conducted by a researcher who remains blind to the patient’s treatment allocation and will be conducted pre and post-treatment and at six and 12 months follow-up. Health care utilisation will be assessed throughout a two year period following entry to the trial. Executive function, rumination and emotion regulation will also be measured to determine the impact of these factors on treatment response in two treatment groups.

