Participants who complete the phone interview and are eligible for the RCT will be told about the trial at the end of the phone interview. Those individuals interested in participating will be sent a participant information statement, consent form and the baseline questionnaires (Short Form (36) Health Survey; SF-36 [46]; Geriatric Anxiety Inventory [47]; Ruminative Response Scale [38]; Emotion Regulation Questionnaire [39]). Upon receipt of their consent form and baseline questionnaires, participants will be randomised, by an independent researcher, into one of three conditions: CBT, PST or E-TAU (described below). Medical files will be accessed to get details of current medications (including anti-depressant medication) and to confirm their diagnoses. Participants will then be contacted by a member of the research team and informed of their condition. If allocated to CBT or PST, the researcher will arrange an appointment for their first therapy session, which will be conducted at a local health clinic. During the first session participants in the PST and CBT conditions will complete the Stroop Interference Task [37].

Treatment consists of 10 one hour weekly sessions. All participants will have their depressive symptoms monitored via the administration of the GDS-SF midway through the trial period (i.e. after 5 weeks). If any individual demonstrates a reliable deterioration [48], from trial entry, in GDS-SF score they will be contacted by the research team to determine their ability to continue the trial and to ensure their safety. Post-treatment assessment using PRIME-MD Depression module, GDS-SF and the HAM-D will be conducted. Participants will also be asked to complete the SF-36 to assess their quality of life and the Geriatric Anxiety Inventory to assess co-morbid anxiety symptoms at post-treatment. Follow-up assessments will be conducted six and 12 months after the trial. Data on health care utilisation will be gained from Medicare and the Pharmaceutical Benefits Scheme in order to determine the cost efficacy of the interventions in the two years following treatment.

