##### Sample size

The primary outcomes are a diagnosis of depression according to PRIME-MD and severity of depression according to the HDS and GDS. In a recent meta-analysis, the average effect size for CBT (including PST trials) was 1.06 and for PST was 1.00 [10]. To be conservative, we have used the smaller ES of 1.00. According to G-power, we would need only 25 participants per group have 95% power to detect a significant difference (p < 0.05) between the 2 active treatments and the control condition [53]. However, we are also interested in the relative efficacy of each of the 2 interventions. Given that these two treatments have never been compared in any clinical setting, we determined that to be conservative, we should power the study to identify even small differences in effect sizes (Cohen’s D = 0.25) between the two treatments. In order to be able to observe a difference between the two groups of 0.25 with 80% power and a significance level of 0.05, we need 59 participants per group. That is, 177 participants in total.

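### The week-5 GDS-SF, taken in all three arms, has no place in the stated mixed model, so people who leave for good before post-treatment add nothing to the GDS-SF analysis, and the contrast is biased if leaving depends on that score differently by arm

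*Protocol article*

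**What the plan says.** The Procedure section of the protocol article schedules a mid-treatment reading in every arm: "All participants will have their depressive symptoms monitored via the administration of the GDS-SF midway through the trial period (i.e. after 5 weeks". Treatment lasts ten weeks ("Treatment consists of 10 one hour weekly sessions"), so this falls halfway. The reading serves as monitoring. For a participant whose score has reliably worsened since entry, the section says "they will be contacted by the research team to determine their ability to continue the trial", and adds a safety purpose.

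The Methods/design paragraph of the Abstract says that the blinded assessments "will be conducted pre and post-treatment and at six and 12 months follow-up". The Statistical analysis section agrees: "There are 4 measurement times, of which 3 are post-intervention". It names the model ("Linear mixed models will be used to account for the hierarchical, non-independent nature of the data") and the role of baseline: "Baseline outcome measures (e.g., HAM-D and GDS-SF) will be used as a covariate". The article gives the week-5 score no role in the analysis.

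The standing of the GDS-SF varies. The second Sample size subsection says "The primary outcomes are a diagnosis of depression according to PRIME-MD and severity of depression according to the HDS and GDS", and the Abstract agrees. Outcome measures names the PRIME-MD diagnosis as primary and lists the GDS-SF as an additional measure.

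**The concern.** A likelihood-based mixed model deals with drop-out through the outcomes and covariates that it contains. If leaving depends on a score that was recorded but left out, the protection expected under missing-at-random is lost for that part of the drop-out. Here the omitted score is the same instrument, taken in all arms, and the article itself links it to a check on whether the person can continue.

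The arms also ask different things of participants: weekly clinic sessions in CBT and PST, and no trial-specified treatment in E-TAU. Selection that differs between therapy and control is therefore plausible, and it could also differ between CBT and PST. At stake is the post-treatment GDS-SF contrast, including the CBT–PST comparison, for which the second Sample size subsection sets 0.25 SD as the difference of interest.

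**Working it through.** **1. The plan's own count.** Pre (1) + post (1) + 6 and 12 months (2) = 4, of which 3 are post-intervention. This reproduces the stated figure. For the GDS-SF alone, adding week 5 gives 5 occasions.

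**2. Who is affected.** With baseline as a covariate, the responses are post-treatment, 6 and 12 months. A person seen at week 5 and never again has no response. Someone who misses post-treatment but returns later still contributes, as does someone who stops therapy but attends assessments. The first Sample size subsection allows 20% attrition (47/0.8 = 58.75, so 59 per arm). That is 0.20 × 59 = 11.8, about 12 per arm, or 0.20 × 177 = 35.4, about 35 in all. It is an upper bound for this group, because attrition can also fall before week 5 or after post-treatment. At 10% the number is 0.10 × 59 = 5.9, about 6 per arm.

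**3. Mechanism.** The documents give no correlations and no drop-out model. Assumed: SD 1; correlations baseline–week 5 0.5, baseline–post 0.4, week 5–post 0.7. The slope of post-treatment on week 5, given baseline, is

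(0.7 − 0.5 × 0.4) / (1 − 0.5²) = 0.50 / 0.75 = 0.667.

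Without week 5, the bias in the contrast is 0.667 times the difference between arms in how far the baseline-adjusted week-5 mean of those who stay has moved. A bias of 0.09 SD thus needs a differential shift of 0.09/0.667 = 0.13 SD at week 5. If the arms shift equally, the bias is zero.

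**4. Simulation.** 59 per arm; true effects 0.3 SD at week 5 and 0.5 SD at post-treatment; log-odds of leaving 1 per SD of the week-5 score; all drop-out placed after week 5. Without week 5: baseline-adjusted regression on those with a post-treatment score. With week 5: the likelihood estimate for monotone missing data, b_T + b_W × a_T. Here b_T and b_W are the treatment and week-5 coefficients for post-treatment among those who stay, and a_T is the treatment effect on week 5 in everyone. Clustering by practice was not modelled. Positive values favour therapy.

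| Who leaves after week 5 | Drop-out | Without week 5 | With week 5 |
|---|---|---|---|
| At random | 20% | 0.503 | 0.504 |
| Equal rates, equal selection in both arms | 20% | 0.500 | 0.501 |
| One common rule in both arms | 20% | 0.485 | 0.50 |
| Worse scorers, therapy arm only | 10% | 0.546 | 0.502 |
| Worse scorers, therapy arm only | 20% | 0.592 | 0.503 |
| Opposite directions in the two arms | 10% | 0.589 | 0.496 |
| Opposite directions in the two arms | 20% | 0.679 | 0.502 |

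Under random drop-out the standard error falls from 0.192 to 0.185 when week 5 is added.

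**5. Sensitivity.** At the protocol's therapy-versus-control effect of 1.00 (0.5 reached by week 5) with 20% drop-out, the therapy-only bias is 0.088 and the common-rule understatement 0.027. Varying the week 5–post correlation from 0.5 to 0.7 and the log-odds from 1 to 2 gives a therapy-only bias of 0.05 to 0.14 SD. For the common rule at effect 1.00, the understatement is 0.02 to 0.07 SD. With week 5 in the model the bias never exceeded 0.006 SD, which is simulation error.

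**The case against.** The strongest reply is that nothing here is inconsistent. The Abstract lists four assessments, the Statistical analysis section counts four, and week 5 is described as monitoring. That stands: a reader who sees five GDS-SF occasions against four measurement times might infer a contradiction, and the documents do not support one. Leaving a monitoring reading out of an efficacy model is common and defensible.

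A second reply is that auxiliary variables and missing-data handling belong in an analysis plan that is not shown. This stands in part. Such a plan could use week 5, and its absence from the article is not the point. The point is that the article does fix the response times, and a better choice is available from data already collected.

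Third, a reader might infer that the estimate is biased whenever early non-responders leave, or that the therapy effect will be overstated. Neither follows. Equal rates and equal selection leave the contrast unbiased. The only link between the week-5 score and continuing in the text is the deterioration check, and it applies in every arm. A single common rule gives a slight understatement. Overstatement needs non-responders to leave the therapy arm selectively, which is plausible but documented nowhere.

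Fourth, the largest figures are extreme. The 0.679 case needs improving controls and non-improving therapy patients to leave, with the whole attrition allowance falling in five weeks; no text supports either. Nor do the documents show how well week 5 predicts drop-out or the post-treatment score.

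Finally, the scope is narrow: there is no week-5 HAM-D or PRIME-MD. Adding a mid-treatment level would also change the planned group-by-time test unless that test is restricted. Both points stand and shape the fix.

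**Conclusion.** The point holds in a conditional form, as an inexpensive improvement and not the correction of an error. The stated GDS-SF model discards the week-5 score of anyone who leaves for good before post-treatment, and the contrast is biased if leaving depends on that score differently by arm.

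Under the assumed correlations and a log-odds of 1 per SD, therapy-only selection gives about 0.04 SD at 10% drop-out after week 5 and 0.09 SD at 20%, the latter an upper bound on the drop-out. This is less than half a standard error (0.09/0.19 = 0.47). It is still about a sixth to a third of the 0.25 SD of interest between CBT and PST (0.04/0.25 = 0.16; 0.09/0.25 = 0.36), should those two arms differ in this way. The bias is about zero under equal rates and equal selection, and an understatement of 0.01 to 0.03 SD under one common rule. Direction and size rest on assumptions that the documents cannot settle. Including week 5 removes the bias in every scenario examined, in all of which leaving depended on nothing beyond the scores included.

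**What to change.** In the Statistical analysis section, state that the GDS-SF model takes the week-5 score in all three arms as an additional response, with categorical time and an unstructured covariance across occasions. State that the treatment contrasts and the group-by-time test stay restricted to post-treatment, 6 and 12 months, so that the planned hypotheses do not change. The week-5 GDS-SF may also serve as an auxiliary variable for missing HAM-D and PRIME-MD values.

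The cost is one more time level and its covariance parameters in one model; no visit or participant is added. The week-5 reading is described as monitoring and is absent from the blinded assessment schedule. The text should therefore say that it informs missing data only and is not an efficacy endpoint.

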### Participants

Consecutive adults aged 65 years and older presenting at GP surgeries will be screened for the study. The inclusion criteria are (1) one or more chronic physical illness; (2) a diagnosis of major or minor depressive disorder or dysthymia; (3) if taking anti-depressant medication, a stable dose for > 8 weeks; (4) have not received electroconvulsive therapy (ECT) within 6 months (to exclude memory problems) and (5) sufficient English to complete questionnaires and take part in therapy. Participants will be excluded if they have (1) suicidal intent requiring emergency care; (2) alcohol or drug abuse or dependence; (3) a history of bipolar disorder or cyclothymia; (3) a psychotic illness; (4) cognitive deficits (< 25 on the Telephone Interview for Cognitive Status [TICS] [42]); or (5) have received psychotherapy within the last six months.

Participants will be recruited at their GP surgery when they attend for an appointment. Based on the prevalence of physical health problems amongst older people (60%) (and depressive symptoms high enough to warrant screening amongst those [30%]), and the likely rate of actual disorder from those who screen positive (70%), we anticipate that approximately 1400 older people will need to be screened in order to achieve the 177 participants required for the RCT.

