### Outcome measures

The primary outcome will be diagnoses of depression according to the PRIME-MD Depression module. In order to allow for multi-modal assessment we will also measure participants’ depression using the GDS-SF [43] and clinician-rated severity according to the HAM-D [45]. Two secondary outcomes will be measured. Quality of life will be assessed with the SF-36 [46] and anxiety will be measured using the Geriatric Anxiety Inventory [47]. These assessments will be conducted by a researcher who remains blind to the participant’s treatment allocation. Blindness will be confirmed by having the independent researcher guess the group that they think each participant belongs to at the end of the treatment period.

As we are interested in which factors affect treatment success, we will also be taking a number of process measures. Executive function will measured using the Stroop Interference Task [37]. For logistical reasons only participants in PST and CBT conditions will be administered the Stroop task because it requires face-to-face administration. The Stroop will be used as a predictor of treatment outcome and not an outcome measures. All participants will be assessed for level of rumination (via the Ruminative Response Scale [38]) and affective regulation (via the Emotion Regulation Questionnaire [39]).

Additionally, demographic variables such as ethnicity and level of education will be recorded, as well as more specific information about previous depressive diagnoses and treatment. In order to confirm details of their chronic illness(es), RCT participants will also be asked to consent to the research team accessing their medical files.

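### The PRIME-MD diagnosis is primary (alone or jointly), but the only model named is linear and no power figure is for a proportion

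*Protocol article*

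**What the plan says.** Three places define what is primary, and they differ.

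- Outcome measures: "The primary outcome will be diagnoses of depression according to the PRIME-MD Depression module". HAM-D and GDS-SF are described as additional measurements, and only quality of life and anxiety are called secondary.
- Abstract, Methods/design: "Primary outcomes will be depression diagnostic status and severity of depression", with HAM-D and GDS given as the severity scales.
- Second Sample size subsection: "The primary outcomes are a diagnosis of depression according to PRIME-MD and severity of depression according to the HDS and GDS".

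The Statistical analysis section names one method: "Linear mixed models will be used to account for the hierarchical, non-independent nature of the data". It tests the group-by-time interaction and uses linear contrasts at time points of interest. On covariates it says: "Baseline outcome measures (e.g., HAM-D and GDS-SF) will be used as a covariate".

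On size, the second Sample size subsection works from a standardised effect: "To be conservative, we have used the smaller ES of 1.00". From this it concludes: "we would need only 25 participants per group have 95% power to detect a significant difference (p < 0.05". It then takes Cohen's d = 0.25 for CBT versus PST and gives 59 per group for 80% power. The first Sample size paragraph gives 47 per group for 95% power, raised to 59 for 20% attrition, with no effect size or outcome attached.

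Eligibility requires "a diagnosis of major or minor depressive disorder or dysthymia".

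**The concern.** Diagnosis is the one outcome that is primary in all three places, and it is binary. A linear mixed model with a common residual variance assumes that outcomes vary equally in all arms. For a binary outcome the variance is p(1−p), so it changes with the remission rate. If therapy and E-TAU differ in remission, a pooled variance is too large for some contrasts and too small for others.

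Two further points follow. Everyone randomised is depressed at entry, so a yes/no baseline diagnosis is the same for all and cannot serve as a covariate. Any baseline adjustment in a model for diagnosis has to come from severity or from the major versus minor/dysthymia stratum used in randomisation. And because no remission rate, risk difference or odds ratio is stated, a reader cannot tell what difference in diagnosis the trial can detect.

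This is more than detail left to an analysis plan. The article fixes a linear model and a standardised-difference basis, and an analysis plan that followed it would carry the mismatch forward.

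**Working it through.** **Inputs from the protocol.** 59 per group; 47 per group after 20% attrition; effect 1.00 versus control; d = 0.25 for CBT versus PST; α = 0.05, taken as two-sided.

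**Assumptions, because the protocol gives no event rates.** Remission means no longer meeting criteria for a depressive diagnosis. Remission in the comparison arm is 10–50% for power. For the variance check it is 60% in both therapies and 10–40% on E-TAU. Arms are equal and clustering by practice is ignored.

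**1. The protocol's own figures, continuous scale.** n per group = 2(z₁₋α/₂ + z_power)²/d².
- d = 1.00, 95% power: 2(1.960 + 1.645)² = 26.0. The stated 25 agrees closely.
- Attrition: 47/0.80 = 58.75, so 59. This agrees.
- d = 0.25, 80% power: 2(1.960 + 0.842)²/0.0625 = 251.2, so 252. The stated 59 does not agree. Power at d = 0.25 is 27% with 59 per group and 23% with 47.

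**2. Power on diagnosis.** A standardised effect is converted by OR = exp(dπ/√3): d = 1.00 gives 6.13 and d = 0.25 gives 1.57. Power is Φ{[|p₁−p₂| − 1.96√(2p̄(1−p̄)/n)] / √([p₁(1−p₁)+p₂(1−p₂)]/n)}.

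Example with n = 47 and 30% in the comparison arm:
- Effect 1.00: odds 0.4286 × 6.13 = 2.63, so p₂ = 0.724. (0.424 − 1.96 × 0.1031)/0.0934 = 2.38, power 99%.
- d = 0.25: odds 0.4286 × 1.574 = 0.675, so p₂ = 0.403. (0.103 − 1.96 × 0.0985)/0.0979 = −0.92, power 18%.

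| Comparison-arm remission | Effect 1.00, n = 47 | d = 0.25, n = 47 | d = 0.25, n = 59 |
|---|---|---|---|
| 10% | 94% | 11% | 13% |
| 20% | 99% | 15% | 18% |
| 30% | 99% | 18% | 21% |
| 40% | 99% | 19% | 23% |
| 50% | 97% | 19% | 23% |

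Converting by a normal cut-point instead lowers the smallest figure for effect 1.00 to 92% and keeps d = 0.25 within 11–23%.

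**3. Detectable difference on diagnosis.** With 47 assessed per arm and 30% control remission, 80% power needs about 58% remission on therapy (0.30 versus 0.583) and 95% power needs 66%.

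**4. Effect of pooling the variance.** With 60% remission on each therapy, p(1−p) = 0.24. The pooled variance is v = [0.24 + 0.24 + t(1−t)]/3, where t is E-TAU remission. The ratio of true to model standard error is √(0.24/v) for CBT versus PST and √([0.24 + t(1−t)]/(2v)) for therapy versus E-TAU. Type I error for CBT versus PST is 2[1 − Φ(1.96/ratio)].

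| t | v | CBT–PST ratio | Type I, CBT–PST | Therapy–E-TAU ratio |
|---|---|---|---|---|
| 10% | 0.190 | 1.124 | 8.1% | 0.93 |
| 25% | 0.2225 | 1.039 | 5.9% | 0.98 |
| 30% | 0.230 | 1.022 | 5.5% | 0.99 |
| 40% | 0.240 | 1.000 | 5.0% | 1.00 |

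A ratio below 1 means that the model overstates the standard error, so the test is conservative.

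**The case against.** The best defence is that two of the three statements of the primary outcome include HAM-D and GDS severity, and for these a linear mixed model and standardised effects are appropriate. That stands. A reader might infer that neither the model nor the power fits the primary outcome at all. The documents support this only for the diagnosis.

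A reader might also infer that baseline adjustment is wasted. The Statistical analysis section names only HAM-D and GDS-SF as examples of baseline covariates and never proposes baseline diagnosis. Adjusting a diagnosis model for baseline HAM-D is compatible with the text. What stands is that baseline diagnosis as yes/no cannot be used, and that the text does not name the randomisation stratum as a covariate.

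A third inference would be that the main hypothesis test is invalid or underpowered. The hypotheses claim superiority of each therapy over control. For that contrast the linear model errs slightly on the safe side, and power is high if the effect of 1.00 holds. That condition matters: the Background itself reports smaller effects in samples with medical illness. At an illustrative d = 0.5, which the protocol does not use, power on diagnosis would be 49–58% with 47 per arm (control remission 20–50%), against 68% on a continuous score.

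Finally, the low power at d = 0.25 is mainly a separate error in the sample size, present on the continuous scale too. The binary outcome only makes it somewhat worse.

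That this is a condensed article does not answer the point, since it names a linear model rather than staying silent.

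**Conclusion.** The point holds in a limited form. The diagnosis is primary in every statement, and solely so in the Outcome measures section, but it has no suitable model and no power basis in the document. The severity scales have a suitable model, and effect sizes on a suitable scale.

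For therapy versus E-TAU the practical harm is modest. The standard error is overstated slightly (true-to-model ratio 0.93–0.99 at 60% versus 10–30% remission), and power is about 94–99% at effect 1.00 with 47 per arm. For CBT versus PST the linear model is anti-conservative, with type I error of about 5.5–8% under the same rates, falling to nominal at 40% E-TAU remission. Power at d = 0.25 is about 11–23% on diagnosis and 23–27% on a continuous score with 47–59 per arm, so the stated 80% is met on neither.

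The type I figures assume a common residual variance without robust standard errors. All diagnosis figures rest on assumed remission rates and ignore clustering.

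**What to change.** 1. Make the abstract, Outcome measures and second Sample size subsection agree on which outcome, or outcomes, are primary.
2. If diagnosis remains primary, name a logistic mixed model, or logistic GEE with robust standard errors. Adjust for baseline HAM-D and the major versus minor/dysthymia stratum, and report the adjusted risk difference and odds ratio.
3. Keep linear mixed models for HAM-D, GDS-SF, SF-36 and the anxiety inventory.
4. Restate the detectable difference on diagnosis as proportions, with the assumed control rate shown. For example, with 47 assessed per arm and 30% control remission: about 58% on therapy for 80% power, 66% for 95%.
5. Withdraw or correct the claim of 80% power at d = 0.25.

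The cost is a few sentences and one restated calculation. No new data are needed: baseline HAM-D is collected in the eligibility interview and the diagnosis stratum is already used in randomisation. Settling this before outcome data are seen also removes any question of choosing the model after the result.
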